## Abstract

**Background:**

Disadvantaged populations face many barriers to cancer care, including limited support in navigating through the complexities of the healthcare system. Family members play an integral role in caring for patients and provide valuable care coordination; however, the effect of family navigators on adherence to cancer screening has not previously been evaluated. Training and evaluating trusted family members and other support persons may improve cancer outcomes for vulnerable patients.

**Methods:**

Guided by principles of community based participatory research (CBPR), “Evaluating Coaches of Older Adults for Cancer Care and Healthy Behaviors (COACH)” is a community-based randomized controlled trial to assess the effectiveness of a trained participant-designated coach (support person or care giver) in navigating cancer-screening for older African American adults, 50–74 years old. Participants are randomly assigned as dyads (participant + coach pair) to receiving either printed educational materials only (PEM—control group) or educational materials plus coach training (COACH—intervention group). We defined a coach as family member, friend, or other lay support person designated by the older adult. The coach training is designed as a one-time, 35- to 40-minute training consisting of: 1) a didactic session that covers the role of the coach, basic facts about colorectal, breast and cervical cancers (including risk factors, signs and symptoms and screening modalities), engaging the healthcare provider in cancer screening, insurance coverage for screening, and related healthcare issues, 2) three video skits addressing misconceptions about and planning for cancer screening, and 3) an interactive role-play session with the trainer to reinforce and practice strategies for encouraging the participant to get screened. The primary study outcome is the difference in the proportion of participants completing at least one of the recommended screenings (for breast, cervix or colorectal cancer) between the control and intervention groups.

**Discussion:**

Building on trusted patient contacts to encourage cancer screening, COACH is a highly sustainable intervention in a high-risk population. It has the potential to minimize the effect of mistrust of the medical establishment on screening behaviors by mobilizing participants’ existing support networks. If effective, the intervention could have a high impact on health care disparities research across multiple diseases.

**Trial registration:**

ClinicalTrials.gov (NCT01613430). Registered June 5, 2012

## Background

Cancer is the second leading cause of death in the United States, and accounts for one in every four deaths [1]. Advances in early diagnosis and treatment have led to declining mortality rates over the past two decades, but racial/ethnic disparities persist [2–5]. By 2030, cancer incidence is expected to increase by 99 % among minorities (vs. 31 % for whites) [6]. Compared to other racial/ethnic groups, African Americans have the highest death rates and shortest survival for most cancers [1, 7]. When stratified by age and race, older African Americans bear the highest mortality burden [8]. Reasons for these ongoing disparities are multifactorial but inadequate secondary prevention through screening and late diagnosis have been shown to play an important role [7, 9–14], highlighting the need for effective and sustainable interventions.

Among the many unique barriers that minority populations face in cancer care are difficulties navigating through the complexities of the healthcare system [15]. The use of care coordination models, including community health workers (CHW) or patient navigators (PN), have demonstrated positive outcomes. These include bridging health care systems and racial/ethnic minority communities in various settings, including for cancer screening [15–19] and diagnostic follow up [18, 20–23]. However, prior patient data revealed that trusted social network members play an even more integral role in caring for patients and may be the most effective at helping to coordinate care and address their cancer-related needs [24, 25]. As care has shifted from the hospital to the home, caregivers have been tasked with complex, multifaceted responsibilities that many are ill prepared to assume [24]. Furthermore, our work with African American older adults suggest that 1) this population considers family and friends as trusted sources of cancer information and 2) both urban and rural African American cancer survivors preferred to work through healthcare access issues with people with whom they already had a relationship (vs. CHWs whom they did not know and who did not have formal health education training) [25, 26]. Additionally, older adult patients are frequently accompanied by family members or other support persons to medical appointments; companions who are verbally active in these visits are generally effective in improving patient-physician communication [27]. As the reliance on family caregivers increases, of noted importance for minority patients, programs to build caregiver confidence and competence provide opportunities to address existing gaps within the healthcare system.

Although a growing body of literature shows the benefits of caregiver-related interventions, there’s limited evidence on their effects on outcomes in cancer care, other than for depression and psychological functioning [28, 29]. To our knowledge, there are no published caregiver-related interventions targeting cancer screening. There is a need for rigorous evidence-based research describing and evaluating interventions where caregivers assist in navigating older adults. The “Evaluating Coaches of Older Adults for Cancer Care and Healthy Behaviors (COACH)” study also addresses the essential need to evaluate the effects of such interventions on caregiver outcomes [30]. The central hypothesis of the COACH study is that members of older adults’ extended families or support networks can be trained to be effective coaches, who provide support through the cancer control continuum (i.e., prevention, screening, diagnosis and treatment). The primary outcome of the study is adherence to cancer screening.

## Methods

### Study design, population and setting

The COACH study is an ongoing community-based randomized controlled trial to assess the effectiveness of trained participant-designated coaches vs. the more standard intervention of distributing printed educational materials in improving cancer-screening behaviors. Participants are randomly assigned as dyads (participant + coach pair) to receiving either printed educational materials only (PEM—control group) or educational materials plus coach training (COACH—intervention group) Fig. 1. The study population consists of African American older adults 50 to 74 years old who reside in Baltimore City or Prince George’s County, Maryland. The populations of both Baltimore City and Prince George’s County are approximately 63 and 65 % African American respectively. Baltimore City’s overall socioeconomic status is lower than that of Prince George’s County as indicated by median household income ($41,385 vs. $73,623) and percent of persons living below the poverty line (23.8 vs. 9.4 %) [31, 32]. Nevertheless, compared to the overall population of the U.S. and of the State of Maryland, both counties show higher age-adjusted cancer mortality rates for breast, cervix and colorectal cancer [33]. The similarities in cancer risk and mortality profiles between these two counties offer a potentially rewarding context for: 1) disaggregating the effects of race/ethnicity vs. socioeconomic status as determinants of adverse health outcomes; and 2) evaluating how the effects of interventions to reduce cancer disparities may vary by socioeconomic status. Other inclusion criteria for the study are: eligibility for breast, cervical or colorectal cancer screening at time of enrollment, and having a support person (coach) who is available to participate in the study. Coaches can be a family member, friend, neighbor or other lay support person designated by the participant. Exclusion criteria include a diagnosis of cancer within the past 5 years or a diagnosis of cancer not in remission, an inability to provide informed consent, or current residence in a chronic care facility or otherwise institutionalized. The rationale for excluding individuals who are institutionalized is that they may already be receiving specific interventions or face special barriers that affect the outcome variables of interest. To preserve the integrity of the trial, only one individual per household is eligible to participate. Randomization is stratified by county and gender.

**Fig. 1 Fig1:**
[figure not shown]
Evaluating Coaches of Older Adults for Cancer Care and Healthy Behaviors (COACH) Study Design Flow Chart

### Recruitment

Participants were recruited into the study between June 2012 and July 2015 using both convenience- and a quasi-population- based sampling. Recruitment began with a cohort of participants from a previous cancer screening study (the Cancer Prevention and Treatment Demonstration (CPTD) Screening Trial control group participants, described in detail here— [19, 34]) who had agreed to be contacted for future studies and were within the age group for the COACH study. These individuals were contacted by phone to determine their interest in and eligibility for the COACH study. Other convenience sampling was conducted in collaboration with our community partners and consisted of targeted outreach events at community centers, churches, senior residential buildings, health fairs, and other events and locations that included our target population. Potential participants were introduced to the study and given the opportunity to be screened for eligibility. The quasi-population-based sampling entailed using commercially obtained rosters of our target population for study recruitment. This data was purchased from Aristotle International, a private company that specializes in compiling and managing voter and consumer information. The data included names and contact information for African American residents of Baltimore City and Prince George’s County, Maryland who were 50–74 years old. These potential participants were initially contacted by letter to introduce the study and provided with an opportunity to opt out of being called for recruitment by study staff. Individuals who did not opt out within a week were then contacted by phone to determine their interest in and eligibility for the study. All potential participants were screened for eligibility by phone (predominantly) or in person. Eligible individuals were consented in person, administered the baseline interview and then randomized 1:1 to either the PEM or COACH group. Participants are enrolled in the study for one year and are administered a 6-month and 1-year follow up interviews. The COACH study was approved by the Johns Hopkins School of Public Health’s Institutional Review Board.

### Interventions

#### Printed educational materials (PEM)

Participants randomized to the control group receive educational brochures on colorectal [35], breast [36] and cervical cancer [37] screenings produced by the National Cancer Institute (breast), Centers for Medicare and Medicaid Services (cervical) and the Centers for Disease Control and Prevention (colorectal).

#### Coach training

Intervention group participants receive the same PEM plus the training of their coaches, a cancer screening reminder postcard 6 weeks after enrollment into the study, and the opportunity to call study staff with any questions related to screening. The coach training is a one-time, in-person, 35- to 40-min training administered to the coach at the time of participant enrollment. Training includes: 1) a didactic session that covers the role of the coach, basic information on colorectal, breast and cervical cancers (including risk factors, signs and symptoms and screening modalities and frequency), how to prepare for a medical visit, discussing cancer screening with a healthcare provider, insurance coverage and no cost screening resources, and related healthcare issues, 2) three video skits (4 min total) addressing misconceptions around cancer screening and working with a healthcare provider and support person to plan for screening, and 3) an interactive role-play session with the trainer to emphasize strategies for encouraging the participant to get screened. The video skits and role-play help reinforce and practice strategies for encouraging the participant to get screened. Coaches are administered a pre- and post- assessment to evaluate change in knowledge and understanding of the material. As part of the training, coaches are given a packet that includes: a copy of the didactic presentation, cancer screening brochures, a points-to-remember sheet to document cancer screening questions for the participant’s healthcare provider and provider recommendations, a suggested task list for the coach, and resources that address well-known barriers to screening such as insurance coverage and transportation. Participants whose coaches disenroll from the study are given an opportunity to have a new support person trained as a coach. To standardize the coach training, all study staff who administer the training are provided with detailed guiding scripts that cover all aspects of the training. Intervention coaches are also provided with information to contact study staff with screening-related questions. Cancer screening guidelines in the coach training are based on recommendations from the U.S. Preventive Services Task Force [38] and the American Cancer Society [39]. These recommendations include: colorectal screening in adults beginning at age 50 (frequency depends on modality), breast cancer screening beginning at age 40 every 1–2 years, and cervical cancer screening beginning at 21 every 3–5 years (with a recommendation for women 65 and over to consult with their doctors). Given the expected diversity in cancer risk among study participants and differences in screening recommendations, the intervention was designed to address individual provider-driven recommendations for cancer screenings (i.e., coaches are encouraged and provided with tools to discuss cancer screening with the participant's healthcare provider).

### Integration of community based participatory research principles

The COACH study is anchored in the principles of Community Based Participatory Research (CBPR) [40, 41]. The study was designed with the active participation of community partners, including representatives of major organizations and health care institutions as well as community members from Baltimore City and Prince George’s County. Participation of community partners occurred at the level of: 1) problem definition and conceptualization; 2) collaborative review of preliminary data; 3) formulation of study hypotheses; 4) development of draft proposal for the study; and, 5) formation of two Community Advisory Groups (one in each study jurisdiction) to oversee the study. The formative phase of the study included key informant in-depth interviews with 12 health practitioners and community leaders within the two counties. Interviews explored the feasibility of the study design, barriers to screening, issues for training participant-designated coaches and providing feedback on the baseline questionnaires. The two broadly representative Community Advisory Groups (CAGs) continue to help guide all phases of the study, including review of study documents. Community Advisory Group members include representatives from community associations, faith-based organizations, local health departments and senior housing facilities, non-profit organizations, local hospitals and clinics, as well as community members.

### Data collection and study measures

All participants (including coaches) are administered a baseline, 6-month and 1-year exit interview. The baseline interview is conducted in person, the 6-month by phone and the exit interview either in-person or by phone. In-person interviews are conducted primarily at participants’ homes or study site located at a community health center. The primary focus of the interview questionnaires is to ascertain information on intermediary and outcome variables for the study, including measures for predisposing, reinforcing, and enabling factors for cancer screening. Under predisposing factors, measures of knowledge, attitudes, beliefs about cancer screening, physical and emotional functional health, cancer risk and past screening behaviors are collected. Re-enforcing factors include measures of trust in the health care system and perceived discrimination—both of which can be powerful predictors of adherence to treatment recommendations [42, 43], satisfaction with care, available support to navigate the health system and perceived self-efficacy to accomplish cancer screening. Enabling factors include items to assess the perceived ease of accessing health care services, the availability and cost associated with care, the perceived ease of scheduling health care appointments, and a standard checklist of co-morbid conditions. Other variables collected include health literacy, cognitive functioning, perceived stress and sociodemographic characteristics (age, gender, ethnicity, race, education, income, marital status and housing situation). Adherence to screening is documented through self-report of cancer screening behaviors; participants’ consent to obtain medical records and Medicare claims data is also obtained. Questionnaire items are based on published literature and uses standard instruments and scales when possible.

### Outcome variables

The primary research question to be addressed by this study is whether the COACH intervention will improve cancer screening adherence compared to the standard (control) PEM intervention. This primary question will be assessed by the difference in the proportion of participants adhering to at least one of the recommended screenings, i.e. mammogram, Pap smear, or colorectal screening. The differences in the cancer screening rates will be examined with both multivariate regression methods and survival analysis, specifically to adjust for withdrawal and right censoring over the study period. Participants who are lost to follow up will be censored at their last visit or interview for the study. Missing data mechanisms (e.g., missing at random (MAR), missing completely at random (MCAR), and non-ignorable missingness (MNAR)) will be evaluated. The distribution of “missingness” will also be assessed by comparing demographic characteristics and baseline outcome variables between participants who completed study questionnaires to those lost to follow up for each intervention arm. To account for missing data, we will consider inverse weighted probability for complete case missing data and multiple imputation methods for item missing data. The analytic strategy will also include methods for handling correlation of repeated measures, such as the Generalized Estimating Equations (GEE) method. All analyses will be carried out according to intention to treat (ITT). Given the study’s focus on provider-driven recommendations for cancer screenings, we included the following additional primary outcome posterior: the difference in the proportion of participants who report talking with their healthcare provider regarding at least one of the recommended cancer screening(s) between the control and intervention groups. Similar statistical methods will be applied here as in the analysis for screening adherence. All statistical models will be adjusted for potential confounders based *a priori* on scientific literature, or exploratory analysis such as bivariate screening.

Secondary outcome variables will include between-group differences in the time to completion of screenings, completion of other preventive screenings, changes in cancer screening barriers, and changes in the reported levels of stress for both the participants and coaches. Several outcomes will also be assessed among the coaches including differences in cancer screening adherence between coaches in the intervention and control groups, predictors of screening at follow up, satisfaction with the intervention, barriers to screening and other outcomes.

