#### Power calculation

The target sample size for the study is 550 participants and 550 coaches (total *N* = 1100 participants). This is the minimum sample size required to show a 13.6 % increase relative to a 35 % anticipated screening proportion among the PEM group during follow up (based on calculations in a similar population from our previous study, the Cancer Prevention and Treatment Demonstration) with a 0.05 two-sided significance level, 20 % Type II error (80 % power), and then taking into account an anticipated loss to follow up of 20 %. Power calculations were performed using STATA/SE 11.2 (Stata Corporation, College Station, TX, USA).

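### A second primary outcome was added later with no stated rank beside screening adherence, so 0.05 is not guaranteed across the two

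*Protocol article*

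**What the plan says.** The protocol article names one primary outcome in two places. The Abstract (Methods) has: "The primary study outcome is the difference in the proportion of participants completing at least one of the recommended screenings". The Background has: "The primary outcome of the study is adherence to cancer screening".

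The Power calculation is built on that outcome alone. It looks for "a 13.6 % increase relative to a 35 % anticipated screening proportion among the PEM group during follow up", "with a 0.05 two-sided significance level, 20 % Type II error (80 % power" with brackets closing there, and then allows for "an anticipated loss to follow up of 20" per cent. The resulting target is 550 participants, each with a coach.

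The Outcome variables section opens with the same primary research question. Later in the paragraph it says: "we included the following additional primary outcome posterior". The addition is the between-group difference in the proportion who report discussing at least one of the recommended screenings with their healthcare provider. The reason given is the study's focus on provider-driven recommendations. Similar methods are to be used. The section gives no testing order, no division of the significance level, and no rule on whether one or both outcomes must succeed.

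**The concern.** The article is not consistent about how many primary outcomes the trial has. There is one in the Abstract, Background and Power calculation, and two in Outcome variables. This is a stated choice about what is primary, not a detail that a condensed article has left out.

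Two things are at stake. First, if a positive result on either outcome at 0.05 counts as a positive primary result, the chance of at least one false positive exceeds 0.05. Second, the two outcomes do not answer the same question. Talking with a provider is a step on the way to screening, and the Coach training section shows that coaches are taught how to raise screening with the provider. It is plausible that this measure moves while screening does not. As written, that result could be reported as a positive primary outcome although the stated primary research question had failed.

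**Working it through.** **Inputs.** From the Power calculation: 35% in the control arm, an increase of 13.6, two-sided 0.05, 80% power, 20% loss. From Recruitment: "randomized 1:1 to either the PEM or COACH group". The documents give no correlation between the two outcomes and no expected rate for provider discussion, so the correlations below are assumptions.

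**Step 1: reproduce the plan's 550.** Read the 13.6 as percentage points, so p1 = 0.35, p2 = 0.486, d = 0.136, mean p = 0.418.

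- Uncorrected n per arm = [z(0.975)·√(2p(1−p)) + z(0.80)·√(p1(1−p1) + p2(1−p2))]² / d² = [1.960 × 0.6975 + 0.8416 × 0.6909]² / 0.0185 = 205.3, rounded up to 206.
- With continuity correction, n′ = (n/4)·[1 + √(1 + 4/(n·d))]² = (205.3/4) × [1 + √1.1433]² = 219.7, rounded up to 220.
- After 20% loss: 220/0.80 = 275 per arm, 550 in total.

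This matches exactly. Without continuity correction the total is 516. Reading 13.6% as a relative increase (35% to 39.8%) gives 4,158 with the correction. So the full two-sided 0.05 was allotted to screening adherence, and nothing was held back for a second primary test.

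**Step 2: familywise error if either outcome can carry the claim at 0.05.** With both null hypotheses true, the error is 1 − P(|Z1| < 1.96 and |Z2| < 1.96), with Z1 and Z2 bivariate normal with correlation r. For r = 0 this is 1 − 0.95² = 0.0975.

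| Assumed r | Familywise error |
|---|---|
| 0 | 0.0975 |
| 0.3 | 0.0951 |
| 0.5 | 0.0907 |
| 0.7 | 0.0835 |
| 0.9 | 0.0704 |

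Whatever the correlation, the sum of the two levels bounds it at 0.10.

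**Step 3: what other decision rules would give.**

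- Screening tested alone: error 0.05, unaffected by any other test.
- Both outcomes must succeed: no inflation. Power for the joint claim cannot exceed that of the screening test.
- Level split to 0.025 each: familywise error 1 − 0.975² = 0.0494 if independent. At 220 evaluable per arm, screening power = Φ[(d − 1/n − z·SE0)/SE1], with SE0 = 0.6975/√220 = 0.0470 and SE1 = 0.6909/√220 = 0.0466. With z = 1.960 this is 80.0%; with z = 2.241 it is 71.2%. Without the 1/n continuity term the figures are 82.7% and 74.4%. Restoring 80% with the correction needs 264 evaluable per arm, or 264/0.80 = 330 per arm and 660 in total.
- Fixed sequence, with screening first at 0.05 and provider discussion only if screening is significant: familywise error 0.05, screening power unchanged at 80.0%, target unchanged at 550.

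**The case against.** The strongest reply is that the article names one primary research question, sizes the trial for it, and nowhere says that success on provider discussion alone would suffice. A multiplicity rule may stand in an analysis plan that is not shown. The addition is disclosed, with a reason that fits the design. Much of this stands, and it rules out several stronger readings that a reader might infer:

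- *That 0.05 fails for the screening claim.* It does not. A test of screening adherence at two-sided 0.05 keeps that error rate. Only a claim resting on either outcome is unprotected.
- *That the error is close to double.* That needs near-independence. Discussing screening and being screened are plausibly positively correlated, which lowers the figure, and a both-must-succeed rule removes the inflation.
- *That the trial has no error control.* The article shows none, but that does not establish that none exists elsewhere.
- *That the outcome was chosen after seeing results.* The text says it was added later, not when or on what knowledge. Recruitment (June 2012 to July 2015) is in the past tense, but the trial is described as ongoing.
- *That the registered question would be displaced.* The article gives only the registration number and date, not the registered outcome.
- *That provider discussion is weaker because it is self-reported.* Data collection says that screening is also documented by self-report. Consent for records and claims is obtained, but the primary analysis is not said to use them.
- *That provider discussion is the likelier of the two to be positive.* Its closeness to the training makes this plausible, but no rate or effect is given, and a high rate among controls could make it harder to shift.

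What the reply does not remove is the conflict within the article. An outcome added later carries the label primary, with no stated relation to the one on which the trial was sized.

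**Conclusion.** The point holds for claims that rest on either of two primary outcomes. If each is tested at 0.05 and either may succeed, familywise error is about 7% to 9.75%, for assumed correlations of 0.9 down to 0; it is above 5% throughout that range. The interpretive risk matters as much as the arithmetic: a positive primary result could be reported on a process measure close to the training content while screening adherence does not improve. The loss of power to 71.2% would arise only under an even split of the level, which the article does not propose and which the fix below avoids. The conclusion rests on the article alone and on the reading of 13.6 as percentage points, which the exact match to 550 supports.

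**What to change.** In Outcome variables, state that screening adherence is the sole confirmatory primary outcome, tested at two-sided 0.05, in line with the Abstract, Background and Power calculation. Then do one of two things with provider discussion:

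- list it as a secondary outcome, marked as added later; or
- test it in fixed sequence at 0.05, only if screening adherence is significant.

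In either case, say that a positive result on provider discussion alone does not make the trial positive. State also when the outcome was added and whether any outcome data had been seen by then. To be credible, the order should be fixed before the unblinded comparison of the arms.

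The cost is wording. The 550 participants, the 0.05 and the 80% power for screening all stay as planned. The one real loss is that provider discussion can no longer carry the trial by itself.

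If the investigators want it to be able to do so, the level has to be divided. With an even split, that means either about 71% power for screening at the planned size or 660 participants, and recruitment is already described as past.

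### The covariates of the two primary comparisons may be chosen by an unspecified exploratory screen, and the randomisation strata and baseline screening history are not committed to the model

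*Protocol article*

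**What the plan says.** All references are to the protocol article.

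- **Outcome variables**, on adjustment: "All statistical models will be adjusted for potential confounders based" either a priori "on scientific literature, or exploratory analysis such as bivariate screening". The two routes are joined by *or*. No candidate list or threshold is given, and the text does not say whether the screen is against outcome, arm or both.
- **Outcome variables**, on method: differences in screening rates "will be examined with both multivariate regression methods and survival analysis". The second primary outcome, talking with a provider about screening, is to be analysed by similar methods, so the adjustment sentence governs it too.
- **Study design, population and setting**: "Randomization is stratified by county and gender".
- **Data collection and study measures**: among the predisposing factors, "cancer risk and past screening behaviors are collected". The same section lists a long set of other baseline measures (attitudes, trust, discrimination, self-efficacy, access, comorbidity, literacy, cognition, stress, sociodemographics).

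Nowhere are county, gender or past screening named as covariates of a primary model. Baseline outcome variables appear only in the comparison of completers with those lost to follow-up.

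**The concern.** In a randomised comparison, covariates serve mainly to gain precision and to reflect how allocation was done. An exploratory search for confounders is an observational-study device. Applied to the primary comparison without a stated rule, it leaves several versions of the primary estimate available after data have been seen, drawn from a large pool of baseline measures. If the analyst may choose among them, the nominal 5% error rate no longer holds.

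The design points to natural covariates. Gender is both a stratum and structurally prognostic: the endpoint is completion of at least one of mammogram, Pap smear or colorectal screening, and men are ordinarily eligible only for the last. Past screening is an obvious predictor of later screening. An open rule stands where these could have been fixed, so the primary model may or may not contain them.

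**Working it through.** **1. The plan's own figure.** Inputs from Power calculation: 35% in the control group, 13.6 points higher (48.6%) under intervention, two-sided 0.05, 80% power, 20% loss. Allocation is 1:1 (Recruitment).

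- n = [1.96·√(2·0.418·0.582) + 0.8416·√(0.35·0.65 + 0.486·0.514)]² / 0.136² = 205.3 per arm.
- Continuity correction: (205.3/4)·[1 + √(1 + 4/(205.3·0.136))]² = 219.7, so 220 per arm and 440 in total.
- 440 / 0.8 = 550, as stated.

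This is an unadjusted two-proportion calculation, so naming covariates does not alter it. The steps below use 220 evaluable per arm.

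**2. Effect of choosing covariates after seeing data.** Two null simulations with 440 evaluable participants. The number and strength of covariates are assumptions, not in the documents.

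*First (3,000 runs, 20 candidate covariates):* each single specification gives type I error 0.049 to 0.053; declaring success if any of four specifications is significant gives 0.070.

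*Second (6,000 runs, 12 candidates including county, gender and history, control proportion about 36%, linear probability model, stratified allocation):*

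| Rule | Type I error |
|---|---|
| Unadjusted | 0.049 |
| County, gender, history fixed | 0.053 |
| Screen on outcome, p<0.2 | 0.053 |
| Screen on arm imbalance, p<0.2 | 0.042 |
| Screen on both | 0.041 |
| Smallest p of these five | 0.074 |
| Set chosen stepwise to minimise the treatment p-value | 0.100 |

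Simulation error is about √(0.074·0.926/6000) = 0.003 for the 0.074 and √(0.07·0.93/3000) = 0.005 for the 0.070. The inflation comes from choosing between results, not from any one screen. One of the five models is unadjusted, which the plan does not propose. The last row is a deliberate worst case.

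Power at about 36% against 49% (2,500 runs): unadjusted 0.79, county, gender and history fixed 0.83, imbalance screen 0.80, outcome screen 0.84.

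**3. If the chosen set omitted the strata.** Assume 70% women, a 13.6-point effect in both genders, and two contrasts in control screening (women/men). Gender alone is used.

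*45%/12%:*
- Overall control rate: 0.7·0.45 + 0.3·0.12 = 0.351.
- Pooled variance: 0.351·0.649 = 0.2278. Within-gender variance: 0.7·0.45·0.55 + 0.3·0.12·0.88 = 0.2049. Ratio 1.11.
- Type I error of the pooled test: 2·[1 − Φ(1.96·√1.11)] = 0.039.
- Under the effect, true SE = √[(0.2049 + 0.2270)/220] = 0.0443; pooled SE = √[(0.2278 + 0.2498)/220] = 0.0466.
- Power omitting gender: Φ[(0.136 − 1.96·0.0466)/0.0443] = 84.3%. Power including it: Φ[(0.136 − 1.96·0.0443)/0.0443] = 86.6%. Loss 2.3 points.

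*40%/23%:*
- Overall control rate 0.349; variances 0.2272 and 0.2211; ratio 1.03; type I error 0.047.
- True SE = √[(0.2211 + 0.2437)/220] = 0.0460; pooled SE = √[(0.2272 + 0.2498)/220] = 0.0466.
- Power 83.5% against 84.1%. Loss 0.6 points.

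**The case against.** The other side has five points.

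- **The a priori route comes first in the sentence.** A reader might infer that the primary model will be data-driven. The text does not say that; it permits it. Permission without a rule is still the defect.
- **Screening need not use outcome data.** A reader might infer that covariates are picked by looking at outcomes. The text does not say what is screened against what, and a screen on arm imbalance alone fits the wording. The supportable criticism is that the rule is unspecified.
- **The plan does not ignore the strata.** A reader might infer an unadjusted analysis with standard errors that are too wide. The plan adjusts all models, and nothing excludes gender, county or past screening. The losses in step 3 are therefore conditional on a set that happens to leave the strata out.
- **A covariate list is commonly left to the analysis plan.** This stands for the missing list taken alone. It does not cover the stated rule, which affirmatively allows exploratory selection in the primary models.
- **Covariates can matter beyond precision, and not every model is randomised.** With 20% loss expected, covariates related to dropout are relevant among those observed. The article also plans predictors of screening among coaches, where bivariate screening is ordinary practice. Both points stand, so the change should be confined to the primary between-arm comparisons.

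**Conclusion.** The point holds in a limited form. The article allows the covariates of both primary comparisons to be chosen by an unspecified exploratory screen and does not commit the strata or baseline screening history. That much follows from the text without assumptions.

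The size is moderate and illustrative. One rule fixed in advance holds type I error near 5% (0.041 to 0.053 in the simulations). About 7% arises only if the analyst picks among four or five adjustment sets, and 10% only under a deliberate search for the smallest p-value. The plan announces neither behaviour, so these figures are not the error rate of the trial as planned. Omitting the strata would act in the other direction: a type I error of 3.9% to 4.7% and 0.6 to 2.3 points of power lost, under gender splits that the documents do not give. The sample size of 550 reproduces and is not in question. This should be corrected, but it does not undermine the trial.

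**What to change.** In Outcome variables, limit the adjustment sentence by type of analysis:

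- For the two primary between-arm comparisons, remove the exploratory-screening route. Name county, gender and baseline screening history (for example, the number of screenings due at enrolment) as covariates, plus any others listed before outcome data are examined.
- Label any further data-driven adjustment of those comparisons as sensitivity or exploratory.
- Keep bivariate screening for non-randomised analyses, such as predictors of screening among coaches.

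The cost is wording only. The strata are known from randomisation, past screening is already collected, and the target of 550 does not change. The article describes the trial as ongoing, so the choice can be recorded before outcomes are analysed.
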